### The Therap-i module

For participants in the experimental group, the Therap-i module is added as a supportive tool to their psychotherapeutic TAU. The Therap-i module involves; i) a resilience interview, ii) the development and initialisation of an ESM diary, iii) ESM monitoring, and iv) three feedback sessions.

First, in the resilience interview, we focus on assessing strengths of the patient. This aspect can be relatively underrepresented in clinical practice because of the primary focus on psychopathological complaints. Personal strengths and resilience factors are inquired by asking questions originating from solution-focused therapy [28]*,* such as “How would you describe yourself as a person before you got sick?”, “Can you describe one or several uplifts in the last month?”

Second, ESM items are developed for each patient individually. Items cover five domains that are important for case conceptualization: affect, behavior, cognition, body, and context. The ESM diary contains items that are assessed multiple times per day and items that are assessed once per day (morning/evening). It includes 22 fixed items (Table S1.1) and up to about ten personalized items. The fixed items are part of the ESM item bank developed in our department for the PErsonalized Treatment by Real-time Assessment (PETRA; www.petrapsy.nl [29];) project. The number of personalized items is flexible, but patients will be advised to limit the total number of items to 30 in order to manage measurement strain [15, 30]. The personalized items are developed in the ESM development session (45 min). Patient, clinician, and researcher collaborate to identify important personal aspects that trigger, perpetuate or influence psychiatric complaints to create the personalized ESM items. The researcher provides suggestions based on information from the electronic patient health record and the resilience interview. The researcher checks whether identified aspects are covered by items in the PETRA item bank. If this is not the case, a new item will be created based on a set of criteria for high-quality ESM items given in the Supplementary Materials S2. After the first and second feedback session (explained in detail below), it is possible to add diary items if new insights were obtained. The session in which the ESM diary is personalized is immediately followed by a 30-min instruction session between the patient and researcher, which also includes a practice run.

Third, patients fill out their personalized ESM diary 5 times a day for 8 weeks. The personalized ESM diary is initiated in a web-based flexible interface on our secured server system Routine Outcome and QUality Assessment (RoQua, [31]). Timing of assessments will be personalized to fit natural wake-sleep rhythm; the first daily assessment will be 2–3 h after waking-up in the morning. The system is programmed to send text messages (beeps) with links to the online questionnaires to the patient’s smartphone. This yields a maximum of 280 data points for the personalized feedback. Patients will be called 48 h after starting with ESM monitoring for motivation and to ask whether they have questions or experience technical problems. Every other day, the frequency of filling out ESM diaries is monitored in RoQua. When more than three subsequent assessments are missed, patients will be contacted to check whether they experience problems. Patients are instructed to complete the ESM diaries as soon as possible after receiving the beep, preferably within 10 min, and that they have limited time to respond. When no response is received, patients will be reminded after 10 min, and the link will be closed after 30 min. During the ESM monitoring period the patient can contact the researcher 24/7 when needed.

Fourth, patients receive personalized feedback during a regular consult with their clinician and the researcher after 2, 4, and 8 weeks of ESM monitoring. Dynamic visualizations of ESM data are provided with in-house developed software for personalized feedback (in R, using packages RMarkdown and Shiny by [name] [32, 33];). In the feedback sessions the focus is on combining quantitative information from ESM rating scales with qualitative (contextual) information from patient-entered text during monitoring. In line with previous feedback report procedures [21, 23], the reports contain increasingly rich information across the treatment period. Patients receive feedback on raw course ESM time-series data after 2 weeks, and after 4 and 8 weeks monitoring additionally feedback on ESM time-series derived network models is available. Detailed information on the feedback module is beyond the scope of the current design paper and described elsewhere ([name] et al., in preparation). A log of the graphs discussed along with notes of the session will be saved as a pdf file and sent to the patient and clinician for reference.

### Study parameters

#### Questionnaire assessments

Figure 1 shows the schedule of questionnaire assessments, and Table 2 provides the instruments used at each wave (T0-T7). All questionnaire were assessed in Dutch. All participants fill out questionnaires over a period of 8 months: before and during the first 8 weeks of their treatment period (T0-T3) and during a follow-up period (T4-T7). Questionnaire data are collected via our secured RoQua web application developed to monitor outcomes in health care and research [31]. Participants receive an email with a link to fill out the questionnaires. When necessary, participants receive a reminder to fill out the questionnaires by email after 2 and 4 days and a call by a research assistant after 4 days.

**Table 2 Tab2:** Overview of instruments

		P	T0	T1	T2	T3	T4	T5	T6	T7
				ESM period						
**Screening/Stratification**										
Mini-SCAN	psychiatric diagnoses	X								
DM-TRD	treatment resistance	X								
**Baseline characteristics and others**										
Questionnaire	demographics, medication, prior treatment		X							
TAS-20	alexithymia		X							
LEIDS-RR	cognitive reactivity		X							
Long-term difficulties questionnaire	long-term difficulties		X							
DAS-A-17	dysfunctional attitudes		X							
CTQ-SF	childhood trauma		X							
Happiness index	happiness		X				X			
Brugha	life events						X			
Single item	medication switches						X			X
Single item (clinician)	type of psychological intervention					X				
**Outcomes**										
IDS-SR	depressive symptom		X	X	X	X	X	X	X	X
OQ-45	psychol. functioning		X	X	X	X	X	X	X	X
WAI-SR	therapeutic alliance^a^			X	X	X	X	X	X	X
IPQ-MH	illness perception		X	X	X	X	X	X	X	X
QSRD	self-management						X			
**Daily assessments**										
ESM^b^	momentary affect and other factors			−5 times a day-						
Actigraphy	physical activity			-continuous-						
**Evaluation Therap-i module**^b^										
Questionnaire	participant evaluation						X			
Questionnaire	clinician evaluation					X				
Interview	participant evaluation						X			

Note: P, pre-baseline; T0, baseline measurement; T1 till T7, follow-up waves (see method section for details); *CTQ-SF* Childhood Trauma Questionnaire Short Form, *DAS-A-17* Dysfunctional Attitude Scale form A, *DM-TRD* Dutch Method for quantification of Treatment Resistance in Depression, *ESM* Experienced Sampling Method, *IDS-SR* Inventory Depressive Symptomatology - Self-Report, *IPQ-MH* Illness Perception Questionnaire Mental Health, *LEIDS-RR* Leiden Index of Depression Sensitivity 2nd Revision, *Mini-SCAN* Mini-Schedules for Clinical Assessment in Neuropsychiatry, *OQ-45* Outcome Questionnaire-45, *QSRD* Questionnaire Self-management in Recovery of Depression, *TAS-20* Toronto Alexitymia Scale-20, *WAI-SR* Work Alliance Inventory Short form Revised. ^a^, WAI-SR is assessed at baseline if the patient already knows their clinician (see method section for details); ^b^ = experimental group only

Outcomes are assessed at all waves with the: i) Inventory of Depressive Symptomatology Self-Report (IDS-SR) to assess depression symptom severity [34–36]; ii) the Outcome Questionnaire (OQ-45) to assess changes in psychosocial functioning within three domains, including symptom distress, interpersonal functioning and social role [37, 38]; iii) Working Alliance Inventory – Short form Revised (WAI-SR) to assess therapeutic alliance between a patient and their clinician [39, 40]; and iv) Illness Perception Questionnaire Mental Health (IPQ-MH) to assess a patients’ perception of their illness with four of its sub-scales, namely, personal control over the problem, control gained in treatment, coherence, and emotional representation [41].

Baseline measurement (T0) includes i) a questionnaire on sociodemographic characteristics (gender, age, education level, work- and living situation), medication use, and past psychotherapy; ii) the Toronto Alexithymia Scale (TAS-20) to assess alexithymia (a subclinical inability to describe emotions), which may influence a participant’s ability to fill out the ESM diaries and thereby possibly influencing the efficacy of the Therap-i module [42–44]; iii) the Leiden Index of Depression Sensitivity - second revision (LEIDS-RR, [45, 46] to assess cognitive reactivity to negative mood to index depression vulnerability; iv) the Long-term difficulties questionnaire (e.g. housing or financial problems), which may partly mediate the severity of depressive symptomatology or interfere with the recovery process [47]; v) the Dysfunctional Attitude Scale (form A) revised (DAS-A-17 [48]; to assess the presence and intensity of dysfunctional attitudes; vi) the Childhood Trauma Questionnaire – Short Form (CTQ-SF) to assess the severity of childhood maltreatment, which may partly mediate the severity and/or chronicity of depressive symptomatology [49]. Some additional measurements are performed including i) the Questionnaire of Self-management in the Recovery from Depression (QSRD) at T4 to assess self-management using a descriptive outcome measure [50]. The QRSD originates from qualitative research in a sample of depressed patients, ii) the Brugha recent life events questionnaire, enriched with positive life events, at T4 to assess important positive and negative life events [51, 52], iii) the happiness index at T0 and T4, which is a single item, used in a large Dutch sample before, to assess a global estimation of how a participant feels in general [53, 54], and iv) information regarding TAU is collected, including medication switches (T3 and T7), applied types of psychotherapeutic treatment (T3 filled out by the clinician), and the number of sessions and treatment length in minutes (T7) collected from the electronic patient health record.

#### Actigraphy assessment

All participants wear an actigraph device (MotionWatch8®) for a period of 8 weeks. Actigraphy measurement starts together with ESM monitoring in the experimental group and is timed to start about 10 days after baseline in the control group to approximately match this timing (also see Fig. 1). Actigraphy data will be used for calculation of day-time activity patterns and circadian rhythms. Patients are instructed to push the button on the actigraph when going to sleep and right after waking up.

#### Qualitative evaluation interview

In the experimental arm only, participants and clinicians will evaluate the Therap-i module. The participants’ evaluation questionnaires include experienced utility of ESM (content, practicality, strain), feedback reports (content, intelligibility, lay-out), and feedback sessions (content, intelligibility). The clinicians’ evaluation questionnaires include the experienced utility of the Therap-i module supporting TAU. Both questionnaires are in-house instruments. Via a semi-structured interview, qualitative evaluations of the Therap-i module are obtained from 20 patients. The interview covers five topics: i) overall evaluation of the Therap-i module, ii) evaluation of the separate components of the Therap-i module, including the resilience interview, filling out the ESM diaries, feedback rapports, and the collaborative discussion based on the feedback rapports with the clinician and researcher iii) obtained insights by patients on their depression and if and how these insights were used in daily life to better manage depressive complaints, iv) influences of the Therap-i module on the psychological treatment, and v) influences of the Therap-i module on the therapeutic alliance.

### Data management

In the Therap-i study, the following types of data will be collected: questionnaire data, ESM data, logistic data, actigraphy data, interview data, personal data and work documents. Questionnaire and ESM-data are collected via the RoQua server [31]. RoQua is a secure web application which makes it possible to measure and monitor outcomes in health care and research. Logistic data will be collected via REDCap (Research Electronic Data Capture; https://www.project-redcap.org). REDCap is a secure web application for building and managing databases. Data collected in REDCap are automatically backed-up on a daily basis on the servers of the Universitair Medisch Centrum Groningen (UMCG). Logistic data concerns all data collected during the execution of research activities. For each procedural step, a digital questionnaire and checklist is built to support data capture and planning of research activities. Actigraphy data will be collected via CamNtech’s MotionWatch and downloaded via the software MotionWare. Interview data originate from the semi-structured interview as part of the qualitative evaluation of the Therap-i module. Personal data concern identifiable data, such as name, date of birth, (email) address, and telephone number. Work documents concern documents that are used in order to create the electronic diary or which contain feedback information discussed during a consult with the patient and therapist. All files are stored on a secured drive on the servers of the UMCG, which is accessible for authorized members of the research team only. Interviews are digitally recorded and the audio files will be transcribed verbatim. Work documents are scanned and stored as pdf-files. Paper versions are stored in a locked cabinet in our department. When the study closes, REDCap will be frozen after verification, all queries have been handled and the close-out visit of the monitor. Data files containing raw data are stored in a password protected folder on the secured drive. These data files as well as the actigraph, interview and personal data files will be locked for editing and contain the date of downloading/saving in their name. After publication of the main results of the study, the processed, pseudonymised data will be made available for re-use via a data transfer agreement.

### Statistical methods

#### Sample size calculation and withdrawal

We performed a sample size calculation for our main hypothesis that adding the Therap-i module to TAU will lead to greater reduction of depressive symptoms (as assessed with the IDS-SR) compared to TAU (G*Power 3.1, F test for repeated measures, within-between interactions [55]. Our power analysis is based on the effect size found in a previous study by Kramer and colleagues [21]. In their pioneer RCT, the authors showed that systematic intensive self-monitoring and personalized feedback on contextualized patterns of positive affect through ESM could provide an effective add-on tool to routine clinical care. IDS-SR scores for the experimental group showed an initial 3-point drop 7 weeks after baseline. While this effect became larger at later measurements, we chose the 7-week measurement as a reference point because it was the smallest post-intervention effect and therefore provided a conservative basis for the power analysis. Given a range of standard deviations of 10.0–10.5, the decrease in IDS-SR scores translates to an effect size of 0.14–0.15 (Cohen’s f). With a sample size of 80 (40 per group), an alpha of 0.05 and an intraclass correlation of 0.5 (between the pre and post repeated measures), and 4 measurement occasions (T0-T3), we have an 85–90% power to detect such an effect. To achieve a realistic estimation of the required sample size, one needs to further account for dropout. In a study from our department that is closely related to the proposed study [22, 23], dropout in the intervention period was 20%. Accordingly, to ensure that we will have at least 40 participants in each treatment arm, we will enrol 50 participants per study arm (total *n* = 100).

Patients can withdraw from the study at any time for any reason if they wish to do so without any consequences. In the case of withdrawal, attempts will be made to follow-up with the patient to establish cause of withdrawal, and to collect qualitative data regarding experience of participation. All data, including those from withdrawn patients (unless they request for their data to be deleted), will be included in the final analysis. If a patient withdraws from the study prematurely without providing valuable data, a replacement participant will be sought if resources allow. In case patients withdraw before randomization, they will be replaced. After randomization they will not be replaced.

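### The f of 0.14–0.15 behind the sample size is not the time-by-group interaction f for a 3-point difference; the stated 85–90% power is about 17–32%

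*Protocol article*

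**What the plan says.** The calculation is in the protocol article, under Statistical methods, Sample size calculation and withdrawal. It serves the main hypothesis, that the module reduces IDS-SR scores more than treatment as usual alone. The procedure is named as "G*Power 3.1, F test for repeated measures, within-between interactions".

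The raw effect comes from an earlier randomised trial of ESM feedback: "IDS-SR scores for the experimental group showed an initial 3-point drop 7 weeks after baseline". The conversion follows: "Given a range of standard deviations of 10.0–10.5, the decrease in IDS-SR scores translates to an effect size of 0.14–0.15", expressed as Cohen's f. The other inputs are given as "With a sample size of 80 (40 per group), an alpha of 0.05 and an intraclass correlation of 0.5", and the result as "4 measurement occasions (T0-T3), we have an 85–90% power to detect such an effect".

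The section calls the week-7 effect a conservative basis because it was the smallest effect after the intervention. It then allows for 20% dropout and arrives at 100 enrolled. The section on efficacy plans a multilevel model with time, group and their interaction, a random intercept and a random slope for time.

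**The concern.** In this G*Power procedure, f is the spread of the group-by-time deviations, after group and time main effects are removed, divided by the SD. It is not a standardised difference at one occasion. Randomised arms are equal in expectation at T0, so a 3-point difference that develops later is split between a group main effect and an interaction. Only the interaction part counts in the named test. An f of 0.14–0.15 looked too large for that part, and it matches half of Cohen's d for a 3-point difference.

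This calculation is the only justification given for the sample size. If the f is too large, the trial has much less power for the effect it names than readers are told. A null result would then be taken as evidence against the module although the design had little chance of detecting the planned effect.

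**Working it through.** **Inputs** (all from the sample-size section): difference 3 points; SD 10.0–10.5; N = 80 (40 per arm); m = 4 occasions; correlation ρ = 0.5; alpha 0.05; k = 2 groups.

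**1. Reproduce the stated power.** The test uses a noncentral F with λ = f²·N·m/(1 − ρ), df1 = (k − 1)(m − 1) = 3 and df2 = (N − k)(m − 1) = 234.

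- f = 0.14: λ = 0.0196 × 80 × 4/0.5 = 12.54, power 85.1%.
- f = 0.15: λ = 0.0225 × 640 = 14.40, power 90.0%.

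This matches the article. G*Power's alternative effect-size conventions give 40–47% for the same f, and two occasions instead of four give 70–75%. So f was entered as the four-occasion interaction effect under this formula.

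**2. Find where f comes from.** 3/(2 × 10.5) = 0.143 and 3/(2 × 10.0) = 0.150. The article shows no formula, but its range is d/2, the f for two means 3 points apart in one comparison.

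**3. Compute the interaction f for 3 points.** Let d₀ to d₃ be the between-arm differences at T0–T3, with d₀ = 0. Each arm deviates by ±(dₜ − mean d)/2, so f = √[mean of ((dₜ − mean d)/2)²]/SD.

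Example, linear growth 0, 1, 2, 3 with SD 10: the mean is 1.5 and the half-deviations are −0.75, −0.25, 0.25, 0.75. Their root mean square is 0.559, so f = 0.0559, λ = 0.0559² × 640 = 2.0 and power is 19.0%.

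The article gives no time course, so several were taken. In each range the first figure is for SD 10.5 and the second for SD 10.

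| Difference at T0, T1, T2, T3 | Interaction f | λ | Power, N = 80 |
|---|---|---|---|
| 0, 1, 2, 3 (linear) | 0.053–0.056 | 1.81–2.00 | 17.5–19.0% |
| 0, 3, 3, 3 (step), or 0, 0, 0, 3 | 0.062–0.065 | 2.45–2.70 | 22.5–24.6% |
| 0, 0, 3, 3 (most favourable) | 0.071–0.075 | 3.27–3.60 | 29.2–32.0% |

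The last row is a ceiling. Values confined to 0–3 have a standard deviation of at most 1.5; half of that is 0.75, and 0.75/10 = 0.075. A grid search over all such patterns gave the same maximum.

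**4. Check the metric.** With two occasions (0, 3) and SD 10, f = 0.075 and λ = 0.005625 × 80 × 2/0.5 = 1.8, power 26.3%. A t-test on change scores has SD of change √(2 × 100 × 0.5) = 10 and squared noncentrality 3²/(10² × 2/40) = 1.8, which is the same. Simulation of the 3-df test at SD 10 (8,000 trials per pattern) gave 19.3%, 24.6% and 31.2% for the three rows.

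**5. What the entered f stands for.** Scaling each pattern until its f equals 3/(2 × SD) gives a maximum difference of 6.0 points (most favourable), 6.9 (step) or 8.05 (linear).

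**6. Other variants, for a 3-point difference.**

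- A 1-df linear time-by-group slope test, closer to the planned model, N = 80 and no random-slope variance: 27–29% (linear), 23–25% (step), 36–39% (most favourable).
- The named test with all 100 patients retained: 21–40% across the patterns.
- Analysed patients needed for 85% power on the named test: 276 to 544.

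The dropout step is correct: 80/0.8 = 100.

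**The case against.** The strongest reply is that 17–32% is conditional. It belongs to a 3-df F test on exactly 80 patients, under assumed time courses. The planned analysis is a multilevel model that also uses data from patients who withdraw. That is fair as far as it goes: a slope test can reach 39% at N = 80, and the named test 40% if nobody is lost. Thus 32% is a ceiling for the named test only. Neither variant comes near 85%, and slope variance between patients, which the planned model allows for, would lower the slope figures.

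A second reply is that the 3 points are described as a drop in the experimental arm, so reading them as a between-arm difference is an assumption. This is also true. If the earlier trial's controls improved as well, the between-arm effect and the power are smaller still. To rescue the stated power, the controls would have had to worsen by about 3 to 5 points, so that the contrast reached 6–8, and the article says nothing of the kind.

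Third, the word conservative refers to the choice of week 7 over later, larger effects. That reasoning about the time point stands. It does not make the power calculation conservative, because the conversion to f doubles the largest interaction effect that 3 points could produce.

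An analysis that is not planned, ANCOVA on the mean of the three post-baseline scores, would give about 51–55%. That too is well short of the claim.

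**Conclusion.** The concern holds, and the figure is wrong as written. The statement "we have an 85–90% power to detect such an effect" is true of an interaction f of 0.14–0.15, but a 3-point difference with SD 10.0–10.5 does not produce that f. For the named test with 80 patients, power for 3 points is about 17–32%. The stated 85–90% needs a between-arm difference of about 6–8 points.

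This rests on equal arms at T0, a between-arm difference that stays within 0–3 points through T3, correlation 0.5 at every pair of occasions, and 80 analysed patients. The position within the range depends on the time course, which the article does not give. The conclusion that power is far below 85–90% does not depend on it.

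**What to change.** Keep enrolment at 100 and rewrite the power statement in one of two ways:

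- State that 80 completers give about 17–32% power on the named test for a 3-point between-arm difference by T3, and name the assumed time course.
- State that 85–90% power applies to a between-arm difference of about 6–8 points, again with the time course.

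In either case, show how f was derived from the cell means, and say explicitly that the 3 points are taken as a between-arm difference. Limit the conservative remark to the choice of the week-7 time point. It would also help, though the correction does not depend on it, to say that a non-significant result will be read through the confidence interval for the T3 difference.

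The cost is a rewritten paragraph, matching wording in the analysis plan if one exists, and a much less favourable stated power. No extra patients and no design change are needed.
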